**B. Study Design**

**Study setting**

Emergency and neurogical and neurosurgical clinic of the University Hospital of Basel

**Inclusion criteria**

1. All consecutive patients who are admitted to the emergency department with an ischemic or hemorrhagic stroke or transient ischemic attach (TIA) according to the World Health organization criteria [37] with symptom onset within the last 3 days.

2. All consecutive patients who undergo intracranial surgery due to

- pituitary tumors

- intracerebral hemorrhage (ICH)

- subarachnoidal hemorrhage (SAH)

- chronic subdural hematoma

- head trauma with contusio cerebri

- intracranial abcesses

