Plasma sodium concentrations are kept within a narrow range to maintain a constant plasma osmolality. This is predominantly regulated by arginin vasopressin (ADH). ADH is produced in the hypothalamus and stored in and released from the neurohypophysis. Plasma ADH levels begin to fall immediately upon swallowing water, before plasma dilution occurs, allowing prompt excretion of diluted urine [24]. Unfortunately, the measurement of circulating ADH levels is challenging, since the mature hormone is very unstable, largely attached to platelets and rapidly cleared from plasma with a half-life of 5 to 15 minutes. ADH is derived from a larger precursor peptide (pre-provasopressin) along with two other peptides, neurophysin II and copeptin. Released in an equimolar ratio, the amount of copeptin mirrors the production of ADH. Plasma copeptin concentration have recently been shown to be an easy to determine, steady parameter [25,26].

ADH plays not only a critical role in osmo-regulation, but also in the regulation of the hypothalamo-pituitary-adrenal (HPA) axis and, thus, reflecting the individual stress response. “Stressors” such as stroke or hemorrhage are strong stimulators of the release of ADH [27]. Accordingly, elevated ADH levels have been reported in experimental ischemia [28,29]. In a small clinical study, patients with stroke had increased ADH levels as compared to controls, correlating with stroke severity [30]. Early prognostic factors to predict in-hospital mortality and medium/long-term outcome in stroke patients are important to guide and tailor early decision on treatment, discharge from the stroke unit and interventions to prevent deterioration of mobility status. Existing prognostic models for stroke often include impractical predictor variables, lack sufficient predictive accuracy and are, thus, not routinely used. In this context, copeptin may be a new prognostic marker and a helpful tool in the early risk stratification of stroke patients.

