**Statistical Analyses**

Basic statistical analyses will be performed as described in the diagnostic study. We will evaluate 18 known predictors (i.e. *age; sex; clinical features* (NIHSS or GCS), *important comorbidities* (coronary artery disease, heart failure, atrial fibrillation, hypertension on admission, previous TIA/Stroke, renal disease, dementia, diabetes); *location of the lesion* (LACS etc.); *stroke subtype by the TOAST criteria*; *therapies* (thrombolysis); *laboratory parameters (*baseline glucose level on admission [46-50], CRP); *body temperature*; *smoking histo*ry), and copeptin levels in our multivariate analysis. All variables will first be tested one by one against the dependent variable unfavorable outcome (defined either as Barthel index <85 or modified Ranking scale 3 to 6) for the presence of a significant association. Only variables significantly associated with the outcome will be assessed in a multivariate model performed separately for each parameter.

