**C Procedures**

**Baseline data collection (Appendix 6)**

Access to data of all eligible patients that are not included into this study is important to avoid a selection bias. Thus, we will collect baseline data and information on inclusion and exclusion criteria in all eligible patients irrespective whether they are or are not included into the study. This will allow the comparison of baseline data of eligible patients who consented to participate with those who did not.

Baseline data collection in patients will be collected by the investigators and contain

a) age

b) gender

c) BMI

d) Medical history items: actual history that preceded the hospitalization; ABCD score in patients with transient ischemic attack (Rothwell [38]**Appendix 7**); family history; relevant co-morbidities also assessed by the charlson index [39] (**Appendix 8**) (i.e. hypertension, previous stroke, previous TIA, ischemic heart disease, atrial fibrillation, diabetes mellitus, renal and liver dysfunction, congestive heart failure, dyslipidemia; comorbidities with the risk of hyponatremia (severe hypothyroidism, glucocorticoid insufficiency, neoplasm, HIV infection); smoking history (pack-years) and status (pack per day); current medication; alcohol consumption (glass and grams per day); time from onset of symptoms to admission.

e) Place of residence: i.e. independent living, defined as living at home or in an old people’s home with or without support of the family circle and/or professional care (the family circle consists of the spouse and/or other important persons who live together with the patient; dependent living, defined as nursing home long-stay department, other hospital [40].

f) Clinical items: physical examination including neurological status, NIHSS (to assess the severity of stroke in stroke patients) and Glasgow Coma scale (GCS [41]); blood pressure, pulse rate, weight, volume status (including skin turgor, jugular venous distension, auscultation, if available flow sheet of fluid intake and loss), body temperature; in neurosurgical patients intracerebral pressure if performed within the routine clinical management.

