**E. Sample Size considerations**

Design

This is a prospective observational study to evaluate Copeptin as a diagnostic and prognostic marker in neurological and neurosurgical patients.

Analysis

Analysis tools

All relevant clinical and laboratory parameters obtained by interview, clinical tests and reviewing of the medical records will be entered into an Excel® database. Statistical Analysis System (SAS® Institute, Cary, NC, USA) and R for Windows (R Foundation for Statistical Computing, www.r-project.org) will be used for data analysis. Statistical evaluation will include stepwise logistic regression analysis to assess which variables are independently associated with outcome.

Sample size considerations

Our sample size consideration is based on our intention to determine an optimal clinical model to predict the outcome of neurological and neurosurgical patients (based on Barthel index, Rankin scale NIHSS scale and Glasgow outcome scale) (i.e. the prognostic question of the study). To determine an optimal clinical model we will undertake a multivariable regression analysis. It has been demonstrated that multiple regression models with a minimum of 10 to 15 observations per predictor variable reveal good estimates [45]. We will evaluate 18 known predictors (i.e. *age; sex; clinical features* (NIHSS or GCS), *important comorbidities* (coronary artery disease, heart failure, atrial fibrillation, hypertension on admission, previous TIA/Stroke, renal disease, dementia, diabetes); *location of the lesion* (LACS etc.); *stroke subtype by the TOAST criteria*; *therapies* (thrombolysis); *laboratory parameters (*baseline glucose level on admission [46-50], CRP); *body temperature*; *smoking histo*ry) in our multivariate analysis. Therefore, we aim to include a minimum sample size of 180 patients (for 10 observations per predictor) to 270 (for 15 observations per predictor) and a maximum sample size of 360 patients (for 20 observations per predictor). All variables will first be tested one by one against the dependent variable unfavorable outcome (defined either as Barthel index <85 or modified Ranking scale 3 to 6) for the presence of a significant association. Only variables significantly associated with the outcome will be assessed in a multivariate model performed separately for each parameter.

Based on the last year’s data in our hospital, the following number of patients with stroke and neurosurgery will be eligible:

*Patients*

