|  | Cases 2003 | Cases 2004 |
| --- | --- | --- |
| Estimated eligible neurosurgical patients | Around 180 | Around 180 |
| Ischemic stroke | Around 300 | Around 300 |

An estimated total of around 480 patients will thus be eligible. With an estimated informed consent of 80% and an estimated loss of follow-up of 10%, approximately 350 patients could be included.

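### Stroke patients may be sampled at any point up to about three days after onset, yet the fixed covariate list has no time-from-onset term although onset-to-admission time is collected

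*Protocol*

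**What the plan says.** Four parts of the protocol bear on this.

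- **Entry window.** Under Inclusion criteria, stroke and TIA patients qualify "with symptom onset within the last 3 days". The neurosurgical criteria have no onset window.
- **Timing data.** Item d of Baseline data collection records "time from onset of symptoms to admission". The interval ends at admission, not at the blood draw.
- **Sampling.** Under Measurement of copeptin concentrations and section D, an extra EDTA tube is kept at routine draws. No time relative to onset is fixed, and no sample is named as the prognostic value. Item h of Baseline data collection deals with food, smoking and posture as influences on copeptin, but not with time since onset.
- **Model.** The prognostic Statistical Analyses section states "We will evaluate 18 known predictors", itemises them, and adds copeptin: "and copeptin levels in our multivariate analysis". Section E repeats the same 18 items. None is a time variable. Only variables with a significant univariable association with outcome go on to the multivariate model.

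The rationale in section 2.1 is that stressors "such as stroke or hemorrhage are strong stimulators of the release of ADH" and that copeptin mirrors ADH production.

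**The concern.** A marker proposed because it reflects the response to an acute insult is naturally read against the time since that insult. As written, the plan analyses a value taken soon after onset and one taken near the end of the three-day window on the same scale, with nothing in the model to tell them apart. If copeptin changes over those days, the part of its variation due only to timing acts as measurement error in the main predictor and pulls its odds ratio towards one. If arrival time is also related to outcome, the two are mixed.

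This is not simply a detail left for a statistical analysis plan. The protocol itself fixes the covariates by name, twice, and derives its sample size from the length of the list. An analysis that follows the list leaves onset time out. Adding it to the candidates would not be enough either: a variable can distort copeptin without being significantly related to outcome, and the univariable filter would then remove it.

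**Working it through.** **1. The plan's own figures.** Counting the list: age, sex, NIHSS or GCS, eight comorbidities, lesion location, TOAST subtype, thrombolysis, glucose, CRP, temperature, smoking = 18. The rule in section E is a "minimum of 10 to 15 observations per predictor variable reveal good estimates". This gives 18 × 10 = 180, 18 × 15 = 270 and 18 × 20 = 360, all as stated. Accrual: 480 × 0.80 × 0.90 = 345.6, against about 350 stated.

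**2. Room for another term, on the same rule.** The eligibility table gives 300 ischemic stroke cases a year: 300 × 0.80 × 0.90 = 216.

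| Terms | Stroke patients per term |
|---|---|
| 18 listed | 216/18 = 12.0 |
| 19 (with copeptin) | 216/19 = 11.4 |
| 20 (with copeptin and onset time) | 216/20 = 10.8 |
| 21 (onset time on two degrees of freedom) | 216/21 = 10.3 |

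All are above 10 and below 15. In the whole cohort, 345.6/20 = 17.3. The table lists no separate TIA or non-surgical hemorrhagic stroke cases, so the stroke/TIA total is approximate.

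**3. Possible size of the effect.** The documents give no copeptin kinetics, so every input here is an assumption: SD of log copeptin s = 0.8; true log-odds slope 0.80 per SD of the time-zero value; onset-to-sample time uniform over 72 h; log-linear fall by a factor F over 72 h.

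- Variance due to timing: v = (ln F)²/12.
- Slope retained, approximately: λ = s²/(s² + v).

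| Fall over 72 h | v | λ | Slope 0.80 × λ | Odds ratio per SD |
|---|---|---|---|---|
| none (F = 1) | 0 | 1 | 0.80 | 2.23 |
| 50% (F = 2) | 0.040 | 0.64/0.680 = 0.94 | 0.75 | 2.12 |
| 75% (F = 4) | 0.160 | 0.64/0.800 = 0.80 | 0.64 | 1.90 |

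Simulated cohorts of 216 with an average-patient risk of 37% (also assumed) agree: unadjusted slopes of about 0.81, 0.76 and 0.64, and 0.81 to 0.82 in each setting once linear time is included. The AUC of copeptin is about 0.70, 0.69 and 0.68, so the loss is about 0.01 to 0.02. The standard error of the unadjusted slope at a 50% fall is about 0.16.

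**4. If patients with higher copeptin arrive earlier (correlation 0.3).** With c = s² + 0.3·s·√v and w = s² + v + 2 × 0.3·s·√v, the retained share is c/w.

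- F = 2: 0.688/0.776 = 0.89, slope 0.71.
- F = 4: 0.736/0.992 = 0.74, slope 0.59.

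The squared correlation between observed and time-zero copeptin, c²/(s²w), is 0.95 and 0.85. That is higher than the 0.94 and 0.80 without the correlation. The slope falls because observed copeptin is more widely spread on a fixed SD scale, not because it discriminates less well.

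**The case against.** - **Copeptin may not decline.** A reader might infer that early and late values are not the same measurement because ADH clears in minutes. The documents do not support that. The half-life of 5 to 15 minutes in section 2.1 belongs to ADH and is given as a reason not to measure it; the same paragraph describes copeptin as steady. A short half-life would not show that secretion falls over three days either. This stands: a decline is an assumption, and no effect at all is within the range.
- **The loss is small where it matters for prediction.** Also right for the AUC. If most patients arrive early (assumed exponential, mean about 12 h), the AUC loss is only 0.002 at a 50% fall and 0.007 at 75%.
- **A bedside tool uses whatever value the patient presents with, so unadjusted performance is the relevant figure.** This is a fair reason to keep reporting it. It is not a reason to omit the adjusted result, because the protocol also asks which variables are independently associated with outcome.
- **Earlier arrival of severe cases is already handled by NIHSS or GCS.** Partly right: severity is on the list, and the simulation leaves it out. A reader might take the slopes of 0.71 and 0.59 as a further loss of prognostic value; step 4 shows that they are not.
- **The study is exploratory and the list names known predictors, not assay modifiers.** True, and it limits the weight of the point. The list is nevertheless the only adjustment set the protocol gives.

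**Conclusion.** The point holds as a gap in the adjustment set for stroke and TIA patients. The three-day window, sampling at routine draws without a fixed time from onset, the collection of onset-to-admission time and its absence from both copies of the covariate list are all plain in the protocol.

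The size is undocumented. It runs from nil to a moderate attenuation: a slope of 0.80 per SD becoming about 0.75 to 0.6 under assumed falls of 50% to 75% over 72 h, with an AUC loss of about 0.01 to 0.02. These figures rest wholly on the assumptions in steps 3 and 4.

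The documents do not show that copeptin's association with outcome will in fact be biased. Nor do they show that the needed variable is fully in hand, since the recorded interval stops at admission. The case for a change is that it is cheap and guards the main predictor against a plausible source of noise or confounding.

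**What to change.** In the stroke/TIA model only:

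1. Force in time from onset, as a linear or flexible term, whatever its univariable p-value. The collected onset-to-admission time will serve at a minimum.
2. Name the admission sample as the prognostic copeptin value and record its draw time, so that onset-to-sample time can be used instead.
3. Report copeptin's odds ratio and AUC with and without this term, and by onset window, for example up to 24 h and 24 to 72 h.

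The cost is one or two degrees of freedom and one extra recorded time. No comorbidity has to be dropped and no patients added: 216/20 = 10.8 per term for one degree of freedom and 216/21 = 10.3 for two, both above the protocol's minimum of 10.

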**Exclusion criteria**

Patients without informed consent.

**C Procedures**

**Baseline data collection (Appendix 6)**

Access to data of all eligible patients that are not included into this study is important to avoid a selection bias. Thus, we will collect baseline data and information on inclusion and exclusion criteria in all eligible patients irrespective whether they are or are not included into the study. This will allow the comparison of baseline data of eligible patients who consented to participate with those who did not.

Baseline data collection in patients will be collected by the investigators and contain

a) age

b) gender

c) BMI

d) Medical history items: actual history that preceded the hospitalization; ABCD score in patients with transient ischemic attack (Rothwell [38]**Appendix 7**); family history; relevant co-morbidities also assessed by the charlson index [39] (**Appendix 8**) (i.e. hypertension, previous stroke, previous TIA, ischemic heart disease, atrial fibrillation, diabetes mellitus, renal and liver dysfunction, congestive heart failure, dyslipidemia; comorbidities with the risk of hyponatremia (severe hypothyroidism, glucocorticoid insufficiency, neoplasm, HIV infection); smoking history (pack-years) and status (pack per day); current medication; alcohol consumption (glass and grams per day); time from onset of symptoms to admission.

e) Place of residence: i.e. independent living, defined as living at home or in an old people’s home with or without support of the family circle and/or professional care (the family circle consists of the spouse and/or other important persons who live together with the patient; dependent living, defined as nursing home long-stay department, other hospital [40].

f) Clinical items: physical examination including neurological status, NIHSS (to assess the severity of stroke in stroke patients) and Glasgow Coma scale (GCS [41]); blood pressure, pulse rate, weight, volume status (including skin turgor, jugular venous distension, auscultation, if available flow sheet of fluid intake and loss), body temperature; in neurosurgical patients intracerebral pressure if performed within the routine clinical management.
g) Clinical symptoms of hyponatraemia will be evaluated on admission and in case of sodium imbalance in neurological patients. In patients undergoing intracranial surgery we will evaluate clinical symptoms daily. Specifically we will monitor the presence of headache, anorexia, nausea, vomiting, muscle cramps and aches, seizures, confusion, apathetic or lethargic development.
h) Routine/Standard laboratory tests: routine blood sampling including: hematocrit, blood urea nitrogen, bicarbonate, total protein, albumin, uric acid serum and urine electrolytes, urine and serum osmolality, creatinine, lipids, TSH, fT4, T3, and basal cortisol. All blood sampling will be done before any food intake, or smoking, if feasible (both, upright position and smoking will potentially elevate ADH and Copeptin levels). Alternatively, influencing factors will be monitored.
i) Imaging : Computer tomography or MRI of the neurocranium (T1, T2, diffusion-weighted image sequence, with or without contrast), if indicated magnetic resonance angiography or conventional cerebral angiography. We will record the time-points of contrast agent application.

Stroke patients will also be classified on the basis of the vascular territory of the ischemic lesion as follows: total anterior circulation syndrome (TACS), partial anterior circulation syndrome (PACS), lacunar circulation syndrome (LACS), posterior circulation syndrome (POCS).

j) Further investigations: Stroke patients will have neurosonography, echocardiography, standard 12-leaf electrocardiography and 24 –hour electrocardiography and then will be classified by etiology of strokes according to Trial of Org 10172 in acute Treatment (TOAST) stroke subtype classification, which differs between large artery atherosclerosis, cardioembolism, small-artery occlusion, other etiology, and undetermined etiology [42].

Importantly, all these investigations are currently performed in the routine setting. Therefore, no additional costs will be charged to the patient, the health care provider or the health insurances.

**Informed consent statement (Appendix 9 a and b,10,11,12)**

The study will be approved by the ethics committee of Basel (Ethikkommission beider Basel). It is important to note that this is an exploratory and observational study; the only study related intervention will be the asseveration of 7.5ml of plasma obtained during the routinely performed blood sampling. Therefore, patients are required to provide written informed consent that they agree for the use of their data for scientific purposes. In patients, in which “informed consent” is not feasible due to sequela of the acute CNS lesion (the latter a prerequisite for inclusion), patients’ next to kin can sign an assent form to state the presumptive will of the patient. In case, next of kin are not readily available, a treating physician – who must not be involved in the study – have to certify that there are no objections for inclusion in the study from his point of view. Only after these informed consent procedures the patient can be included in the study.

**Management of participants throughout the trial**

Step 1. All eligible patients in the emergency department or the neurological ward or the neurosurgical ward will be included into the study.

Step 2. All baseline data will be collected.

Step 3. During hospitalization we Clinical items including weight, blood pressure, pulse rate, volume status and body temperature will be assessed by chart review until discharge. In neurosurgical patients, we will monitor intracerebral pressure if performed within the routine clinical management.

- Fluid treatment and drugs

- Potential symptoms of hyponatremia, i.e. headache, nausea, vomiting, muscle cramps and aches, anorexia, impaired consciousness, seizure **(Appendix13)** [9].

- Routinely performed laboratory tests (chemogramm, plasma glucose, serum osmolality, urine osmolality, sodium in urine, hematocrit) will be sampled at the time-points when blood sampling is routinely done on the wards.

Step 4. In all patients, on day 5 of the hospitalization, a clinical examination with GCS, NIHSS, Barthel Index and Ranking Scale will be performed.

The future place of residence (i.e. dependent vs. independent living) will be assessed.

Step 6. In patients with ischemic stroke a telephone follow-up **(Appendix 14)** regarding morbidity and mortality (as assessed by the Barthel Index and Ranking Scale) will be obtained after 3 months. An unfavorable outcome will be defined as a Barthel index <85 or modified Rankin scale of 3 to 6 [43].

Patients after neurosurgery will have a telephone follow-up **( Appendix 15)** after 3 months to evaluate mortality, relapse, and quality of life as assessed by the Glasgow outcome scale [44] and Barthel index.

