#### 1. SYNOPSIS

**Background:**

Sodium imbalance is common and an adverse prognostic factor in hospitalized patients. However, identifying the causes of sodium imbalance is challenging in clinical practice. Levels of antidiuretic hormone (ADH) are elevated in patients with stroke correlating with disease severity and stress level; however, its measurement is cumbersome. ADH is derived from a larger precursor peptide along with Copeptin, which is a more stable peptide directly mirroring the production of ADH. Copeptin can be assayed readily in plasma. Early prognostic factors to predict in-hospital mortality and medium/long-term outcome in critically ill neurological patients, are helpful to guide and tailor early decisions on treatment, discharge from the intensive care unit and application of interventions to prevent deterioration of neurological functions.

**Aim:** To evaluate Copeptin as a diagnostic tool in disturbances of water homeostasis and prognostic tool to predict outcome in a well-defined cohort of stroke patients and patients undergoing intracranial surgery.

**Design:** Prospective, observational study.

**Location Setting:** Emergency and neurogical and neurosurgical clinic of the University Hospital of Basel.

**Patients:** Neurological patients with ischemic and hemorrhagic stroke and patients undergoing intracranial surgery.

**Intervention:** After informed consent, all routinely determined baseline data will be assessed including medical history, clinical items (i.e. neurological status, volume status, pulse rate, blood pressure, weight) and laboratory items (i.e. urine / serum osmolality, electrolytes, among others). All patients will have a follow-up with clinical and laboratory assessment until the day of discharge. After 3 months, they will be followed-up by a structured telephone interview to assess outcome (mortality, morbidity, as assessed by the ranking scale and Barthel index). Copeptin will be assessed in a batch analysis upon completion of the plasma asseveration.

**Variables and measurements:** Baseline data on medical history and clinical items, co-morbidities and treatment procedures will be collected. This exploratory study will be conducted over a 12 month period from November 2006 to November 2007.

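### The protocol's sections disagree on who is called at 3 months and on which scale, so the model's unfavourable outcome is not defined alike for all enrolled patients

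*Protocol*

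**What the plan says.** **Who is enrolled.** Protocol, Inclusion criteria, item 1 takes patients "admitted to the emergency department with an ischemic or hemorrhagic stroke or transient ischemic attach (TIA"). Item 2 takes "All consecutive patients who undergo intracranial surgery due to" a list of conditions that includes intracerebral and subarachnoid haemorrhage.

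**Who is called, and on which scale.**
- Synopsis, Intervention: the paragraph refers to all patients and says "they will be followed-up by a structured telephone interview to assess outcome (mortality, morbidity, as assessed by the ranking scale and Barthel index").
- Prognostic question in patients with stroke: Barthel and Rankin at day 5 and at 3 months, for stroke patients without restriction to ischaemic stroke.
- Prognostic question in neurosurgical patients: Glasgow outcome scale and Barthel at day 5 and at 3 months, with no Rankin.
- Management of participants, Step 4: Barthel and Rankin on day 5 in every patient.
- Management of participants, Step 6: "In patients with ischemic stroke a telephone follow-up" with Barthel and Rankin. Neurosurgical patients are called "after 3 months to evaluate mortality, relapse, and quality of life as assessed by the Glasgow outcome scale" and Barthel, again with no Rankin.

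**The outcome that is modelled.** The Statistical Analyses of the Prognostic Study and section E both give the dependent variable as unfavourable outcome, "defined either as Barthel index <85 or modified Ranking scale 3 to 6". Section E says the model is to serve neurological and neurosurgical patients together. It lists the Glasgow outcome scale among the scales on which outcome is based, but the binary definition gives that scale no cut-off.

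**The concern.** Step 6 is the operational instruction and is tied to the call forms. Staff who follow it as written would not call a TIA patient or a patient with a non-operated haemorrhagic stroke, and would not ask a neurosurgical patient the Rankin questions. Whether a 3-month outcome exists, and on which scale, would then depend on diagnosis.

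The sample size is built on the prognostic model, so this is the study's main regression outcome. A later analysis plan can choose between scales or add a coding rule. It cannot supply a call that was not made or a scale that was not asked once the 3-month window has closed.

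**Working it through.** **1. The protocol's own figures.** Section E gives about 180 eligible neurosurgical patients and about 300 with ischaemic stroke, 80% consent and 10% loss to follow-up.
- (180 + 300) × 0.80 × 0.90 = 345.6, against the stated approximate 350. This reproduces.
- 18 predictors × 10, 15 and 20 = 180, 270 and 360. These reproduce exactly.

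**2. Scales at 3 months, by enrolled group.**

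| Group | Synopsis | Prognostic questions | Step 6 |
|---|---|---|---|
| Ischaemic stroke | Rankin, Barthel | Rankin, Barthel | Rankin, Barthel |
| Haemorrhagic stroke, not operated | Rankin, Barthel | Rankin, Barthel | not named |
| TIA | Rankin, Barthel (through the all-patients wording) | not named | not named |
| Intracranial surgery | Rankin, Barthel | Glasgow outcome scale, Barthel | Glasgow outcome scale, Barthel |

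Only the ischaemic stroke row agrees across all three places.

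**3. Neurosurgical patients without a planned 3-month Rankin.**
- Share of the projected cohort: 180/480 = 37.5%.
- Number after consent and loss: 180 × 0.80 × 0.90 = 129.6, about 130 of 346.
- Remaining stroke patients: 300 × 0.80 × 0.90 = 216.

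If Rankin were the outcome of the pooled model, 216/18 = 12.0 observations per predictor would remain, against 345.6/18 = 19.2 for the whole cohort. At the minimum size of 180 with the same mix, 180 × 0.625 = 112.5 would remain, or 112.5/18 = 6.25 per predictor, below the protocol's own floor of 10. These last figures apply only if Rankin is the scale chosen.

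**4. Haemorrhagic stroke and TIA patients outside Step 6.** Section E's table has rows for neurosurgery and ischaemic stroke only. It gives no count for non-operated haemorrhagic stroke or TIA, so the number affected cannot be computed. These patients would also come on top of the 480, which would lower the 37.5% somewhat.

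**5. Deaths.** The Rankin range in the definition runs to 6, so a stroke death is unfavourable by rule. In neurosurgery the 3-month call records mortality, the Glasgow outcome scale and Barthel. Of these, only Barthel <85 enters the definition, and the text shown gives no Barthel value for a patient who has died. If *either … or* means two alternative outcomes rather than a composite, the same gap affects a Barthel-only outcome in stroke.

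**The case against.** Several stronger readings are tempting, and the document does not support them.

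- *Haemorrhagic stroke and TIA patients have no 3-month assessment.* A reader of Step 6 alone might infer this. But the Synopsis plans the call for all patients, and the stroke objective plans it for stroke patients in general. What exists is a contradiction. TIA is the weaker case, since only the Synopsis wording covers it.
- *The most severe strokes are lost.* Intracerebral and subarachnoid haemorrhage are listed surgical indications, so operated cases receive the neurosurgical call. Nothing says the non-operated ones are the most severe.
- *Deaths cannot be counted.* Both Step 6 calls record mortality. The gap is a missing rule in the outcome definition. Nothing says deaths are to be excluded, so a bias towards survivors is possible but not built into the plan. The scale and call-form appendices are not shown and might contain a rule.
- *37.5% of patients have no usable endpoint.* Barthel is in both Step 6 calls, so a scale common to those two groups exists.

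It can also be said that the cohorts have separate prognostic questions with their own scales, that the unfavourable-outcome definition in Step 6 stands in the ischaemic stroke paragraph, and that the predictor list contains stroke-specific items. That would excuse different scales if the model were confined to stroke. Section E, however, names both populations for the model. Finally, a death rule is something an analysis plan commonly supplies. That is fair for the rule, but not for the calls and the scale, which are data collection. The exploratory, observational nature of the study lowers the stakes but does not resolve the contradiction.

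**Conclusion.** The point holds as an inconsistency in outcome collection and definition. The sections disagree on who is called at 3 months and on which scale. Step 6 omits two enrolled groups, against the Synopsis and, for haemorrhagic stroke, against the stroke objective. Neurosurgical patients, 37.5% of the projected cohort or about 130 of 346, have no 3-month Rankin in either operative section, against the Synopsis, although they are scored on day 5. The binary outcome for them rests on Barthel alone, and a death is unfavourable by rule only where Rankin is collected.

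The 37.5% rests on section E's eligible numbers and on equal consent and loss in both streams. The size of the haemorrhagic stroke and TIA group and the number of neurosurgical deaths are not given, so neither effect can be quantified. The direction of any bias in the copeptin association is not established by the document.

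**What to change.** 1. Reword the first paragraph of Step 6 to cover all patients with ischaemic or haemorrhagic stroke or TIA, in line with the Synopsis and the Inclusion criteria.
2. Add the Rankin scale to the neurosurgical 3-month call, as the Synopsis already states. The Glasgow outcome scale can stay as an additional neurosurgical outcome.
3. Replace *either … or* in the Statistical Analyses of the Prognostic Study and in section E, and the matching sentence in Step 6, with one 3-month definition of unfavourable outcome on a scale collected in every patient. Rankin 3 to 6 or Barthel <85 would each serve; the documents do not require one over the other.
4. State in that definition that death by 3 months always counts as unfavourable.

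The cost is one amendment, a few more telephone calls, and one question set added to a call already planned. The Synopsis already promises both the calls and the scale. The change concerns outcome assessment only and must be in place before 3-month follow-up starts.
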